### 4.2. Control Group Arm

Each patient in the control group will receive the usual clinical care from their respective nurse in the primary care setting for the duration of this study. The usual clinical practice involves addressing users’ requirements and delivering interventions that can have a positive impact on FOF and/or falls. These activities/interventions are based on the Portfolio of Standardized Services of the Autonomous Community of Madrid, which includes these patients due to their age or as a consequence of their chronic conditions, while detailing the steps to be taken by healthcare professionals.

The nurse will provide structured frailty reversal education in a six-monthly action plan to those patients assigned to the control group, in whom the nurse detects risk of frailty-induced falls (SPPB score below 10, Barthel score between 91 and 100). This action plan will be the one proposed in the Portfolio of Services of the Primary Care Management Board: nutrition, moderate sun exposure, multicomponent physical exercise, fall prevention, and maintenance of intellectual activity and social relations, as well as review of the prescribed treatment, appropriate use of medication, and adherence to treatment. In the case of moderately dependent patients (Barthel score between 61 and 90), the nurse will provide them with a six-monthly action plan covering the proposed structured education: nutrition, physical exercise, fall prevention, and use of mobility aids, as well as review of the prescribed treatment, appropriate use of medication, and adherence to pharmacological treatment.

Figure 1 shows the CONSORT flowchart of participants. Patients participating in this study will not be able to participate in any other study involving educational interventions while this study is ongoing. Patients participating in this study will only be with-drawn from it should they meet withdrawal criteria or no longer wish to participate. No specific treatments have been considered that would preclude continuation in this study.

### 4.3. Visit Plan

During the study period, both study groups will make the following visits (see Table 2):-Initial visit: screening.-Pre-intervention baseline visit: Collection of data on variables. Approximate duration: 60–80 min. The patients assigned to the control group shall carry it out up to two weeks before the beginning of the initial health education intervention.-Five initial sessions with the intervention group.-Visit post initial intervention (visit window: ±4–8 weeks after randomization (for the control group) or ±2 weeks after the initial sessions (for the intervention group)): Collection of data on variables. Approximate duration: 25 min.-Visit at six months post initial intervention (visit window: ±2–4 weeks, at six months after randomization (for the control group) or after the initial health education intervention (for the intervention group)), always prior to the booster session. Collection of data on variables. The structured education plan proposed in the Portfolio of Services will be reviewed in both groups, as well as in the patients in the intervention group, including a follow-up of the issues identified during the health education intervention. Approximate duration: 45 min.-Booster session with the intervention group.-Visit at 12 months (visit window: ±2–4 weeks, at 12 months post randomization in the control group or at 6 months after the booster session in the intervention group). Collection of data on variables. Approximate duration: 20 min.

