#### 2.11.1. Primary Outcome Variable

The seven-item short FES-I scale (Spanish adaptation) scores will be collected at baseline, one month, six months, and one year after the health education intervention. The scale is validated for use with Spanish speakers, with a range of 7–28. A score equal to or greater than 11 is considered positive for FOF (see Table 1). The short FES-I scale showed a Cronbach’s alpha of 0.88 compared to the long version. In addition, the short FES-I obtained a Spearman’s rho correlation coefficient of 0.99 between T1 (measurement at baseline) and T2 (measurement at one month), as well as an intraclass correlation coefficient of 0.77 between T1 and T2 [32].

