#### 2.11.2. Secondary Outcome Variable

Data on the incidence of falls at one month, six months, and one year after the health education intervention will be collected.

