#### 2.11.3. Explanatory Variables

Sociodemographic variables: sex, age, marital status, number of cohabiting individuals, level of education, personal net monthly income, current or previous occupation, availability and type of support at home, perceived ability to receive family support, neighborhood, basic healthcare district, the Medea index (used to measure social inequalities in Spain), time spent in the neighborhood in years, housing characteristics, most frequent type of housing in the neighborhood, accessibility to basic services, perceived safety and walkability of the neighborhood.Functional variables: the Downton scale, the Barthel index, the SPPB scale total score, four-meter gait disturbance, balance disturbance, loss of lower limb strength, the Lawton-Brody index, physical activity recommended for this age group by the Spanish Ministry of Health (i.e., 150 min of moderate physical activity or 75 min of vigorous physical activity; balance exercises; muscle strengthening exercises; flexibility exercises). Data on this variable will be collected separately, and patients will be considered as meeting the recommended physical activity level, provided that 75% of the activities are carried out. This will include a variable regarding how many dimensions (from one to four) are met by the patient.Clinical variables: falls in the previous year (pre intervention); falls during intervention; fall-associated injuries (pre intervention, during intervention, and post intervention); mild visual problems or use of glasses; mild hypoacusis, either unilateral or corrected with a hearing aid; use of a walking device; pain (using a verbal numerical scale); anxiety (via the Generalized Anxiety Disorder-7 (GAD-7) questionnaire); depression (via the Patient Health Questionnaire-8 (PHQ-8); ability to practice self-care (via the Appraisal of Self-Care Agency Scale-Revised (ASA-R)); cognitive level (using the Mini-Mental State Examination); perceived health status; body mass index; urinary incontinence, comorbidities (using the Charlson index); medication; polypharmacy; high blood pressure; nursing diagnosis of risk of falling.Usual footwear variables: heel height in centimeters, type of sole, sole material, type of fastening.Feasibility and acceptability variables:○Feasibility (to be measured among professionals): recruitment rate, randomization, adherence to the health education intervention, follow-ups performed, safety/adverse events, difficulties in implementing the health education intervention. To be assessed at the end of the clinical trial.○Acceptability (to be assessed in patients assigned to the intervention group):-Participants: at the end of the health education intervention, data on its utility, usability, satisfactoriness, recommendability, as well as other open questions will be collected.-Professionals: data on the utility, usability, and satisfactoriness of the program, as well as their readiness to repeat it and other open questions will be collected.

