### 4.1. Intervention Group Arm

The health education intervention will consist of five initial group sessions, plus a reinforcement session after six months. The sessions will be two hours long and will preferably be held once per week. Each group will have approximately 15 participants. The contents detailed in Supplementary File S2. Educational program for nurses in the intervention group will be addressed.

The sessions will include nursing interventions aimed at improving participants’ knowledge, skills, and attitudes regarding their functional ability, fall prevention measures, anxiety management, and ability to cope with FOF and falls.

The activities to be performed during the intervention were drawn from standardized nursing interventions listed in the Nursing Interventions Classification (NIC) following a review of effective interventions addressing these issues [3,4,9,18,33]:NIC 1665. Functional ability enhancement.NIC 5612. Teaching: prescribed exercise.NIC 6490. Fall prevention.NIC 6486. Environmental management: safety.NIC 4700. Cognitive restructuring.NIC 5820. Anxiety reduction.NIC 5230. Coping enhancement.

To monitor the degree of compliance with the interventions as instructed in the protocol, ad hoc questionnaires will be sent after each session to all the professionals and patients who carry out the intervention in order to assess acceptability, feasibility, and satisfaction.

Health education workshops are a fundamental tool for teaching health education in the primary care setting. This workshop was designed following the methodology recommended by the Madrid Primary Care Management Board and is being reviewed by the Validation Commission for Educational Projects of the Community of Madrid (COVAM) for its free distribution throughout the Autonomous Community of Madrid.

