## Figures and Tables

**Figure 1 healthcare-12-02510-f001:**
[figure not shown]
CONSORT flowchart of participants.

**Table 1 healthcare-12-02510-t001:** Short FES-I scale.

Short FES-I Scale How Concerned Are You About the Possibility of Falling While…?	Not at All Concerned	Somewhat Concerned	Fairly Concerned	Very Concerned
1. Getting dressed or undressed	1 □	2 □	3 □	4 □
2. Taking a bath or shower	1 □	2 □	3 □	4 □
3. Getting in or out of a chair	1 □	2 □	3 □	4 □
4. Going up or down stairs	1 □	2 □	3 □	4 □
5. Reaching for something above your head or on the ground	1 □	2 □	3 □	4 □
6. Walking up or down a slope	1 □	2 □	3 □	4 □
7. Going out to a social event (e.g., religious service, family gathering or club meeting)	1 □	2 □	3 □	4 □
SUBTOTAL:	Add all the 1’s	Add all the 2’s	Add all the 3’s	Add all the 4’s
	Short FES-I ≥ 11: Fear of falling			

**Table 2 healthcare-12-02510-t002:** Summary of visits and variables.

Variables	Visits						
	Initial Visit. Screening	Pre-Intervention Baseline visit ^1^	Five Initial Group Sessions	Visit Post Initial Intervention ^2^	Visit at Six Months Post Initial Intervention ^3^	Booster Session	Visit at 12 Months ^4^
Review of eligibility criteria	x						
Informed consent	x	x					
Primary outcome variable: Short FES-I		x		x	x		x
Secondary outcome variable: Post intervention falls		x		x	x		x
EXPLANATORY VARIABLES							
Sociodemographic variables		x					
Functional variables		x			x		
Usual footwear		x			x		
Clinical variables		x					
Falls during intervention				x		x	
Ability to practice self-care		x		x	x		x
Perceived health and anxiety		x		x	x		x
Acceptability (among patients)				x			

^1^ ±2 weeks before the health education intervention (for the intervention group: (IG)). ^2^ ±2 weeks after the initial sessions (IG). ±4–8 weeks after randomization (for the control group (CG)). ^3^ ±2–4 weeks, at six months after randomization (CG) or after the initial health education intervention (IG), always prior to the booster session. ^4^ ±2–4 weeks, at 12 months post randomization (CG), at six months after the booster session (IG).

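### Follow-up visits run on different clocks in the two arms, so time at risk for falls and the timing of the short FES-I differ by arm at visits that the analysis treats as simultaneous

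*Protocol article*

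**What the plan says.** Section 4.3 (Visit Plan) gives each follow-up visit two definitions, one per arm:

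- First follow-up visit: "4–8 weeks after randomization (for the control group) or ±2 weeks after the initial sessions (for the intervention group".
- 6-month visit: "at six months after randomization (for the control group) or after the initial health education intervention (for the intervention group)), always prior to the booster".
- 12-month visit: "at 12 months post randomization in the control group or at 6 months after the booster session in the intervention group".

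The footnotes to Table 2 repeat this; for the last visit they read "at 12 months post randomization (CG), at six months after the booster session (IG".

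The outcomes are defined on one clock for everybody. Section 2.11.1 collects the short FES-I at baseline and "one month, six months, and one year after the health education intervention", and Section 2.11.2 collects falls "at one month, six months, and one year after the health education intervention". Section 4.4 compares the arms at 1, 6 and 12 months. Falls are analysed by a fixed-effects logistic model and reported as odds ratios; no term for length of exposure is mentioned.

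Section 2.11.3 lists among the explanatory clinical variables "falls in the previous year (pre intervention); falls during intervention". Table 2 has a row for these falls separate from the falls outcome. It is marked at the visit after the initial sessions and at the booster session.

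**The concern.** Control participants have no intervention from which to count months, so randomization stands in for it. In the intervention arm the clock starts only when the course ends. It restarts at the booster, which itself comes after the 6-month visit. Visits carrying the same label therefore lie at different distances from randomization.

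For a binary outcome such as having fallen, longer observation alone raises the proportion with an event. An odds ratio without allowance for exposure then mixes the treatment effect with the difference in observation time. The document does not say whether falls during the course belong to the outcome, or which control period corresponds to the course. Both the size and the direction of the distortion depend on that rule. For the short FES-I, the arms are measured at different times since randomization, which matters if scores drift over time.

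**Working it through.** The protocol gives no figure for exposure by arm, so there is none to reproduce. Its sample size (120 evaluable, 150 recruited) is not in dispute and does not depend on this point.

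**Inputs from the protocol**

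- Five sessions (Section 4.1): "The sessions will be two hours long and will preferably be held once per week". First to last session is therefore 4 weeks.
- Time origins: Section 4.3 and the Table 2 footnotes.
- Annual fall incidence p = 0.30 to 0.40 in those over 65 (Section 1).
- Randomization follows consent of all participants (Section 4.5).

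**Assumptions, because the protocol states neither delay**

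- s = wait from randomization to session 1: 0–2 weeks.
- b = wait from the 6-month visit to the booster: 0–4 weeks.
- Constant hazard, the same in both arms; nominal visit dates; the first intervention visit read as 0–2 weeks after the last session.

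**Step 1. Weeks from randomization to each visit**

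| Visit | Intervention | Control | Ratio |
|---|---|---|---|
| First | s + 4 to s + 6, i.e. 4–8 | 4–8 | largely overlapping |
| 6-month | s + 4 + 26 = 30–32 | 26 | 1.15–1.23 |
| 12-month | s + 4 + 26 + b + 26 = 56–62 | 52 | 1.08–1.19 |

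Even with s = b = 0 the gap is 4 weeks at both later visits.

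**Step 2. Odds ratio with no treatment effect**

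The risk of at least one fall by week w is P(w) = 1 − (1 − p)^(w/52). The null odds ratio is the odds of P at the intervention exposure divided by the odds of P at the control exposure.

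*Rule A: falls counted from randomization in both arms.*

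| Comparison | p = 0.30 | p = 0.40 |
|---|---|---|
| 30 vs 26 weeks | 0.1860 vs 0.1633, OR 1.17 | 0.2553 vs 0.2254, OR 1.18 |
| 32 vs 26 weeks | 0.1971 vs 0.1633, OR 1.26 | 0.2697 vs 0.2254, OR 1.27 |
| 56 vs 52 weeks | 0.3189 vs 0.3000, OR 1.09 | 0.4231 vs 0.4000, OR 1.10 |
| 62 vs 52 weeks | 0.3464 vs 0.3000, OR 1.24 | 0.4561 vs 0.4000, OR 1.26 |

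The ranges are 1.17–1.27 at 6 months and 1.09–1.26 at 12 months, both against the intervention. If s is 4 weeks, the largest values are 1.36 (34 vs 26 weeks) and, with b = 4, 1.31 (64 vs 52 weeks).

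*Rule B: only post-session falls count in the intervention arm; control counted from randomization.*

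- 6 months: 26 vs 26 weeks, OR 1.00.
- 12 months: 52 + b vs 52 weeks. b = 0 gives 1.00; b = 4 gives 56 vs 52, OR 1.09–1.10.
- First visit: at most 2 weeks vs 4–8 weeks. 2 vs 4 gives about 0.50; 2 vs 8 gives about 0.24. This favours the intervention.

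The first-visit figure rests on few events. At p = 0.35 and 75 per arm, the expected fallers are 75 × 0.0164 = 1.2 against 75 × 0.0326 = 2.4 to 75 × 0.0641 = 4.8.

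**Step 3. Effect on a real benefit under Rule A**

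At p = 0.35, a true hazard ratio of 0.70 corresponds to an odds ratio of 0.65 at equal 52-week exposure. With 56–62 weeks in the intervention arm it would appear as 0.71–0.80.

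**Step 4. Short FES-I**

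The gap since randomization is 4–6 weeks at the 6-month visit and 4–10 weeks at the 12-month visit, and small at the first visit. The documents give no time trend in the score, so no bias can be computed.

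**The case against.** The strongest reply is that the hypothesis in Section 2.2 is framed at six and 12 months post intervention, so anchoring the intervention arm on the end of the course answers the question asked. If falls are counted the same way, exposure is nominally equal at 6 months and nearly so at 12. This stands, and it limits the size of the problem under that rule. It does not remove it: control still has no counterpart to the end of the course, the booster delay still lengthens the last interval, and the first visit becomes the unequal one.

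Other points also carry weight. Falls are the secondary outcome in Sections 2.1.2 and 2.11.2, although the abstract lists them as primary. Under Rule A the distortion works against the intervention, so it would not create a false benefit. It is also modest beside sampling error: a log odds ratio of about 0.09–0.23, against a standard error of about 0.55 with 60 per arm, 35% incidence and a design effect of 2.1 borrowed from the FES-I calculation. An unseen analysis plan may specify person-time or exact counting windows. The two clocks, however, are stated here twice, and an analysis plan cannot re-date visits already made.

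The visit windows of ±2–4 weeks do not answer the point, because they apply around both targets and add spread without removing the shift. The mixed models in Section 4.4 include time, but nothing says this is actual time since randomization.

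A reader might infer that the plan breaks intention-to-treat or hides exercise-related falls. The documents do not support either. Table 2 records falls during the intervention at the post-initial visit, which both arms attend. Section 2.11.3 also lists injuries from such falls and adverse events, and nowhere is it said that these falls are discarded in one arm. The gap is an undefined counting rule.

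**Conclusion.** The concern holds. As written, the plan gives the arms unequal follow-up at visits it treats as simultaneous, under either way of counting falls. The shift at the 6- and 12-month visits is at least about 4 weeks from randomization.

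Its consequence for falls depends on the counting rule. From randomization, the null odds ratios of 1.17–1.27 and 1.09–1.26 run against the intervention. With post-session counting in the intervention arm, the later visits are close to fair and the imbalance sits mainly at the first visit, in the intervention's favour and on very few fallers. These values rest on a constant hazard, the 30–40% incidence, and the assumed waits before session 1 and before the booster.

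It would go too far to say that the falls odds ratio must differ from 1 at every visit, since one counting rule gives about 1.00 at 6 months. It would also go too far to say that the FES-I comparison is shown to be biased: its timing differs by arm and bias is plausible, but the documents do not allow it to be quantified.

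**What to change.** - **One time origin for visits in both arms.** Either use randomization or, to keep the post-intervention hypothesis, give each control facility an index date equal to a scheduled end-of-sessions date. Time the 12-month visit from that same origin and not from the booster. Use the same windows in both arms.
- **One counting period for falls.** Count falls over the same period in both arms, including the session period, as outcome events. Do not collect outcome falls at the booster session, which only one arm attends.
- **Time at risk.** Account for actual time at risk in the falls model, for example with a person-time offset in a rate model.
- **First-visit label.** Reconcile the one-month outcome label in Sections 2.11.1 and 2.11.2 with the window of ±2 weeks after the sessions in Section 4.3.

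With a common origin the nominal exposure ratio and the null odds ratio both return to 1.00, and the sample size is unchanged. The cost is an amendment to Sections 2.11, 4.3 and 4.4 and to Table 2, and re-dating of visits. If randomization is chosen, intervention participants are seen somewhat sooner after their last session than now. The change should come before follow-up visits take place, because visit dates that differ by arm cannot be fully repaired in the analysis.

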### 2.7. Sample Size

We expect to be able to recruit ten PCFs (five assigned to the intervention group and five to the control group). Assuming a significance level of 0.05, a difference of 3.8 points on the Short Falls Efficacy Scale-International (FES-I), a standard deviation of 5.1 points, and an intraclass correlation coefficient of 0.1, at least 12 participants will be required per center (a total of 120 participants) to reach a power of 80%. Allowing for a loss of 20%, the necessary sample size will be 150 individuals (75 patients assigned to the intervention group and 75 to the control group; approximately 15 patients in each PCF, about five patients per nurse).

Patients seen by nurses at each participating facility and meeting the eligibility criteria will be recruited using a consecutive sampling method until the required sample size—which will be the same for all participating facilities—has been reached.

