## 4. Detailed Procedure

This study has two arms, an intervention and a control arm. Participants from PCFs assigned to the intervention arm would receive the group educational intervention, while participants from PCFs in the control group would receive care as usual. Participants will be assessed for eligibility based on the inclusion and exclusion criteria at the nurses’ office. In cases where the patient agrees to participate and meets the criteria, a screening visit will be conducted to confirm compliance. Screening sheets will be kept for those participants who do not meet the criteria or do not wish to participate.

Patients will be followed up for 12 months. Data collection visits will take place at baseline, one month, six months, and 12 months.

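### Outcome visits run on a different clock in each arm, so falls are compared over unequal or undefined periods, and the direction of the bias depends on a counting rule the protocol does not fix

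*Protocol article*

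**What the plan says.** Section 4.3 (Visit Plan) gives each follow-up visit two starting points.

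- First visit: 4-8 weeks after randomization for controls; within two weeks of the end of the initial sessions for the intervention arm.
- Six-month visit: "at six months after randomization (for the control group) or after the initial health education intervention (for the intervention group"), and always before the booster.
- Final visit: "at 12 months post randomization in the control group or at 6 months after the booster session in the intervention group".

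Table 2, footnotes 2 to 4, repeats these anchors. Section 4 states simply: "Patients will be followed up for 12 months".

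For the baseline visit, Section 4.3 says: "The patients assigned to the control group shall carry it out up to two weeks before the beginning of the initial health education intervention". Table 2, footnote 1, places the visit "2 weeks before the health education intervention (for the intervention group: (IG"), that is, it gives the rule to the other arm.

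Sections 2.11.2 and 4.4 define the falls outcome as falls after the intervention at 1, 6 and 12 months. Section 2.11.3 lists falls during the intervention as a separate clinical variable. Section 4.4 compares the arms by logistic regression and odds ratios and mentions no term for time at risk. Section 4.5 places randomization after consent from all participants, hence before the sessions. Section 4.1 describes five sessions, preferably weekly.

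**The concern.** Randomization makes the arms comparable at the same elapsed time from a common origin. Here the same visit label means a different elapsed time in each arm. The intervention clock starts only when the sessions end, and it is restarted once, at the booster.

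The consequence is mechanical for falls. The chance of at least one fall grows with time at risk, so unequal periods give an odds ratio different from 1 even if the intervention does nothing. The control arm has no intervention, so the phrase post intervention gives it no start date. Whoever counts the falls must supply one, and that choice decides which arm the bias favours.

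Reducing falls is the first secondary objective (Section 2.1.2), and the abstract lists fall incidence among the primary outcomes. An analysis plan cannot move visits that have already been made on two clocks.

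**Working it through.** **The plan's own figure.** The protocol gives no figure for falls or for unequal follow-up. Its one calculation is the sample size in Section 2.7, with a difference of 3.8, SD 5.1 and "an intraclass correlation coefficient of 0.1". The design effect is 1 + (12 - 1) x 0.1 = 2.1, and the effective n is 60/2.1 = 28.57 per arm. Power (two-sided 0.05, normal approximation) is Φ(3.8/(5.1 x √(2/28.57)) - 1.96) = 0.804, and 120/0.8 = 150. This reproduces the stated 80% and 150, and the present point does not affect it.

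**Timing at nominal targets, in weeks from randomization.** Let s be the wait from randomization to session one and b the lag from the six-month visit to the booster. The protocol states neither; both are assumptions. Five weekly sessions span 4 weeks.

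| Visit | Control | Intervention |
|---|---|---|
| Six months | 26 | s + 4 + 26 = 30 + s |
| 12 months | 52 | s + 4 + 26 + b + 26 = 56 + s + b |

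For s of 0-2 and b of 0-2, the offset between arms is 4-6 weeks at six months and 4-8 weeks at 12 months.

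**Fall risk.** The Introduction gives an annual incidence p of 30-40% in people over 65. With a constant hazard, risk(w) = 1 - (1 - p)^(w/52). Both arms get the same hazard, so any odds ratio (intervention/control) other than 1 comes from time alone.

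**Rule 1: falls count from the last session (intervention) and from randomization (control).** This is the closest reading of post intervention, because falls in the session period are recorded separately.

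- First visit, 2 v 4-8 weeks. For p = 0.30 the risks are 0.014 v 0.027 (OR 0.50) to 0.014 v 0.053 (OR 0.24). For p = 0.40 they are 0.019 v 0.039 (0.50) to 0.019 v 0.076 (0.24). This favours the intervention. If the visit took place four weeks after the last session, as the one-month label suggests, the range would be 0.49-1.00.
- Six months, 26 v 26 weeks: OR about 1.0.
- 12 months, 52 + b v 52 weeks: OR 1.00 for b = 0, about 1.05 for b = 2, and 1.09-1.10 for b = 4.

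**Rule 2: falls count from randomization in both arms.**

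| Visit | Offset (weeks) | OR, p = 0.30 | OR, p = 0.40 |
|---|---|---|---|
| Six months | 4 | 1.17 | 1.18 |
| Six months | 6 | 1.26 | 1.27 |
| 12 months | 4 | 1.09 | 1.10 |
| 12 months | 8 | 1.19 | 1.20 |

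This runs against the intervention. With a 5-week offset, a true rate ratio of 0.8 would show at 12 months as an OR of about 0.85 instead of 0.76-0.77.

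**Against sampling error.** With 75 per arm at 35% and no clustering, SE(log OR) = √(2 x [1/(75 x 0.35) + 1/(75 x 0.65)]) = 0.342, so the 95% interval spans a factor of exp(1.96 x 0.342) = 1.96 either side. An OR of 1.10 is 0.095/0.342 = 0.28 standard errors; 1.20 is 0.182/0.342 = 0.53. With a 5-week offset under Rule 2, the two-sided false-positive rate at 12 months is about 6% (60-75 per arm, unclustered).

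**With a common clock** the periods are equal and the null OR is 1.00 at every visit.

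**The case against.** The strongest reply is that the outcome is post-intervention falls, with session-period falls kept apart. Counting from the last session then gives equal time at six months and nearly equal time at 12 months. The stated primary variable is the short FES-I, a point-in-time score that a shift of some weeks affects only if it drifts. Handling time at risk can be left to an analysis plan, and Section 4.4 already includes models with time.

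Much of this stands. It limits the size at 12 months and leaves the FES-I effect unquantified. It does not repair the first visit, where the same reading produces the largest distortion, nor does it give controls a start date. A time term built on visit labels does not help when the label means different elapsed time by arm. Person-time modelling could correct fall exposure if dates are kept, but it cannot move the visits.

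A reader might infer three stronger claims that the document does not support.

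- **That every intervention participant is seen later.** The windows of ±2-4 weeks apply to both arms. At ±4 weeks, controls can be seen in weeks 48-56 and intervention participants from week 52 + s + b, so the windows overlap whenever s + b is 4 or less. Weekly sessions are only preferred. The window centres differ; individual visits need not.
- **That the bias always runs against the intervention.** That requires counting from randomization, which the protocol does not describe. On the closer reading the first visit favours the intervention.
- **That null odds ratios reach 1.4 or more.** That needs a wait of around eight weeks before session one, which is hard to square with Table 2: footnote 1 puts the intervention baseline about two weeks from the sessions, and consent is marked at screening and at baseline, with randomization after consent.

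**Conclusion.** The concern holds in a limited form and should be fixed. The differing anchors are explicit and appear twice. At nominal targets they give different times since randomization, and under either counting rule at least one planned falls comparison has a null odds ratio other than 1.

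The largest effect on the closest reading is at the first visit (about 0.24-0.50), where few falls are expected. At 12 months the bias is modest (1.00-1.10, or 1.09-1.20 if counted from randomization) and well within sampling error for 150 participants, but it is systematic. These figures rest on a constant hazard, 30-40% annual risk, weekly sessions, and assumed values for the wait before session one and the booster lag.

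The documents do not support reading this as a demonstrated bias in the FES-I analysis, because they give no figure for drift. The baseline discrepancy is a separate contradiction between Section 4.3 and Table 2, footnote 1. It may be a slip in arm labels, but the two must be reconciled.

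**What to change.** In Section 4.3 and Table 2, footnotes 1 to 4:

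1. At randomization, set one index date per facility by the same rule in both arms: the planned last-session date for intervention facilities and a matched date for control facilities.
2. Time the 1-, 6- and 12-month outcome visits from that date, with the same windows in both arms, and do not re-anchor the 12-month visit to the booster.
3. State one baseline rule for both arms.
4. Record actual visit dates, and count falls over the same period in both arms.

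Timing every visit from randomization itself is not advisable, because the 1-month visit could then fall inside the session programme: with a two-week wait, the last session is at week 2 + 4 = 6.

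The cost is wording and footnotes, with no added visits; sessions and booster are unchanged. Control facilities need an assigned index date, and the intervention arm's last visit may come slightly less than six months after the booster.
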